#### Content of the intervention program

The tailored RTW intervention program will start with an introductory interview between the participant and an assigned coach from the re-integration agency. Prior to the introductory interview, the participant will be asked to fill out an additional introductory questionnaire. This questionnaire is specifically designed for the coach to obtain insight in the participant’s motivation regarding RTW, needs for additional therapy (e.g., physical and/or psycho-educational), and the skills and knowledge of the participant regarding work and job application processes (e.g., the skill to write letters of application). The results of this questionnaire will be used as input for an introductory interview and to construct a work profile for the participant. During the interview, obstacles and possibilities for RTW and other forms of activities will be identified. Also, the coach and participant will work together during the interview to tailor the participant’s intervention program. There will be several options (or ‘routes’) to tailor the intervention. The possible routes are displayed in Figure 2.

**Figure 2 Fig2:**
[figure not shown]
**Routes in the tailored RTW intervention program.**

#### Routes in the intervention program

First, the coach will decide, together with the participant, whether or not the participant is ready to RTW, or needs additional support and preparation in order to RTW.

#### Route 1

The participant is ready to RTW at the time of the introductory interview. The coach will contact the researchers to independently assign a job hunting agency to this participant. The job hunter will invite the participant for a meeting to explore job opportunities, thereby taking the participant’s work profile into account. Job hunters will always explicitly ask for a participant’s permission to inform future employers of the participants’ history of cancer. Based on the work profile, the job hunter will start a search for at least two jobs, fitting the profile. These jobs should be for at least three months and may include (1) working in paid employment, or (2) working in temporary employment, i.e., this type of work can be arranged with therapeutic conditions and ongoing benefits. The job hunter will have to find jobs within four weeks after the meeting with the participant. If the job hunter is unable to find these jobs, then the second job hunting agency involved in this study will also be invited to search for jobs for the participant. This involvement includes transfer of confidential information about the participant. The participant will be informed thoroughly about this procedure. Also, the participant can use the established work profile to look for jobs independently, alongside the job search with the job hunter. The total search time for a job will be three months. If both job hunting agencies do not find a suitable job for the participant by then, or if the participant is not able to RTW, then the intervention program will end. The participant will still receive usual care by the SSA during the entire follow-up period.

If the job hunter finds a suitable job, the job hunter will stay in touch with the participant during the remaining period (up to three months) of the intervention program, to monitor whether the participant’s RTW is successful and satisfactory. If applicable, the participant can continue to work in the new job after the intervention program has been completed.

#### Route 2

The participant needs support and preparation to RTW. The coach and participant can explore several topics for coaching. After the introductory interview, the participant will receive four sessions of coaching on chosen themes, e.g., how to deal with fatigue or changed life priorities, how to combine work and family, et cetera. As the intervention program continues, the coach and participant will gradually develop a work profile, which will incorporate the participant’s capabilities, needs and preferences for a workplace. After completing the work profile, the coach and participant will decide whether or not the participant is ready to RTW (Route 2A or Route 2B).

#### Route 2A

The participant is ready to RTW. The participant will continue as described in Route 1. If the participant needs support at the workplace, the participant may receive five additional sessions of coaching while being in the process of RTW.

#### Route 2B

The participant needs more preparation to RTW. The participant will receive five additional sessions of coaching on chosen themes. After this, the coach and participant will again decide whether or not the participant is ready to RTW (Route 3A or Route 3B).

#### Route 3A

If the participant is ready to RTW, the participant will continue as described in Route 1.

#### Route 3B

If the participant is not ready to RTW, the intervention program will be terminated.

In Route 2, both 2A and 2B, the coach can also opt for additional support, for example support from a physical therapist and/or psychologist, in case specific physical and/or mental problems are present. If this is the case, the coach will discuss this with the participant’s expert team at the SSA and/or the participant’s GP.

### Completion of the intervention program

The total duration of the program in the most extensive route (2B followed by 3A) will be six to seven months. Here, the participants will receive preparation to RTW for a maximum of four months, including ten sessions of coaching, job application preparation and possibly recovery support, such as physical therapy, and placement in a workplace for a minimum of three months. In general, we anticipate that duration of the program will vary between participants. Some participants will need the most extensive route, and others may need less support in order to facilitate their RTW. Also, in case of extraordinary circumstances, participants can put their tailored RTW intervention program on hold for a period of one month maximum. The limit of one month was chosen to allow for the program to be tailored to each participant’s needs, while maintaining a relatively similar duration of most participants’ programs. We will monitor the chosen route(s) for each participant. During the program, members of the SSA team, as well as the GP, will be notified of the program’s start, progress and finish. They will receive a copy of the intervention plan and the evaluation report.

### Outcome measures & prognostic factors

Data regarding primary and secondary outcome measures, as well as prognostic factors such as sociodemographic factors (i.e., age, gender, level of education), disease-related and work-related factors will be collected using questionnaires. If possible, additional data regarding usual care will be collected from the participant’s file at the SSA. The primary outcome measure of this study is duration until sustainable RTW after sick leave, calculated as the number of days between the day of randomisation and the first day of sustainable RTW. Sustainable RTW is defined as a period of minimum 28 calendar days, during which the CS is working according to schedule. Work can be either paid work or work resumption with ongoing benefits, e.g., work with therapeutic conditions. Recurrences of sick leave within four weeks of RTW will be considered as belonging to the initial period of sick leave, in accordance with the requirements of the Dutch Sickness Benefits legislation. The secondary outcome measure of this study is rate of RTW, i.e., the proportion of participants in each group that sustainably returns to work. Rate of RTW will be not only obtained from questionnaire data, but also, if possible, from participants’ files at the SSA. We will collect data on a number of prognostic factors:**Intention to RTW** will be measured using the ‘Attitudes-Social influence-self-Efficacy’ questionnaire (ASE) [25]. This questionnaire was designed to assess intention to RTW in a study of unemployed persons with common mental disorders. The questionnaire has not been validated. Therefore, its results will be used as an indicator for intention to RTW;**Readiness to RTW** will be measured using the Readiness to RTW Scale (RRTW) [26]. The items on the scale are related to the five stages of change described in the Transtheoretical model by Prochaska and DiClemente [27]. We will adjust the Scale to the Dutch situation as there is no validated translation available, and use the results of this scale as an indicator of readiness to RTW, instead of a validated outcome measure;**Fatigue** will be assessed with the 13-item self-reported FACT-Fatigue Scale (Version 4) [28]. Fatigue is measured in this questionnaire on a four-point scale (range 0–52). It has a high internal validity with a Cronbach’s alpha of 0.96 and high test-retest reliability (ICC = 0.95) [29];**Psychological distress** will be assessed with the Centre for Epidemiological Studies Depression Scale (CES-D) [30-32]. The CES-D is a 20-items questionnaire, measured on a four-point scale. It is designed to measure depressive symptomatology in the general population and has a high reliability with a Cronbach’s alpha of 0.79-0.92 and a test-retest score of 0.90;**General participation in society** will be measured using the Utrecht Scale for Evaluation of Revalidation and Participation (User-P) [33]. The User-P scale aims to rate objective and subjective participation in persons with physical disabilities and consists of 31 items in three scales: Frequency, Restrictions, and Satisfaction. Internal consistency of the USER-Participation scales is moderate to good, with Cronbach’s alpha ranging between 0.70 and 0.91. Spearman correlations between these scales range between 0.36 and 0.52. Test-retest reliability of the User-P scales was measured using the intraclass correlation coefficient (ICC). The ICC of the USER-P was 0.65 for the Frequency scale, 0.85 for the Restrictions scale, and 0.84 for the Satisfaction scale;**Coping** will be measured using the Utrecht Coping List (UCL) [34]. The UCL has 47 statements covering seven coping strategies, such as active problem solving, seeking social support and depressive reaction, and is scored on a four-point scale. Its reliability varies between 0.43 and 0.89, depending on the subscale used. The test-retest score ranges from 0.45 to 0.85, depending on the subscale used;**General health and quality of life** will be assessed with the European Organisation for Research and Treatment of Cancer Quality of Life Questionnaire (EORTC QLQ C-30 version 3.0) [35]. This 30-item list incorporates nine multi-item scales: five functional scales (physical, role, cognitive, emotional and social); three symptom scales (fatigue, pain, nausea and vomiting); and a global health and quality of life scale. The test-retest score has shown to be high for all functional scales with a range of 0.82 to 0.91, and a reliability score over 0.80 for four out of five scales, with cognitive functioning scoring 0.68 [36];**Health-related quality of life** will be measured using the EuroQol 5D scale, developed by the EuroQol group (EQ-5D) [37]. The EQ-5D consists of 5 scales: Mobility, Self-care, Usual activity, Pain/Discomfort, and Anxiety/Depression, with a scale of three levels per item (i.e., no problem, some problems, and extreme problems). The EQ-5D is a generic instrument and has been used in cancer research in numerous studies. Furthermore, a visual analogue scale is provided (range 0–100) to assess overall health state;**Limitations experienced at work** will be measured in participants who have returned to work during the follow-up period, using the Work Limitations Questionnaire (WLQ) [38]. The WLQ consists of 25 items, which describe four dimensions of limitations: limitations in handling time, physical, mental and interpersonal limitations. The questionnaire was tested in two field trials, and the four scales achieved Cronbach’s alphas of > 0.90.**Occupational impact of sleep** will be measured in participants who have returned to work during the follow-up period, using the Dutch Occupational Impact of Sleep Questionnaire (OISQ) [39]. The OISQ consists of 24 items, which aim to assess the effect of sleep quality on work performance. The OISQ has been validated in the Dutch population, correlating highly with other validated sleep questionnaires (coefficients range 0.28 to 0.43, P < 0.0001) and has a high reliability score (Cronbach’s alpha of 0.96). This measure was added as studies have demonstrated that sleep disturbances are common in CSs and that they are related to poorer physical and emotional health, concentration problems (for example at work), and difficulty coping with stress [40].

### Process evaluation

A process evaluation will be conducted to examine the tailored RTW intervention program regarding feasibility, satisfaction, and barriers and facilitators for implementation. The process evaluation will be designed according to the RE-AIM (Reach, Effectiveness, Adoption, Implementation, and Maintenance) framework [41]. The measurements of the process evaluation will be based on: (1) data regarding study procedures and adherence to study protocol, and (2) data collected using additional process evaluation questionnaires, which will be designed separately for participants, team members from the SSA, the re-integration agency and the job hunting agencies.

### Sample size

As a starting point for calculating the sample size, we chose a Hazard Ratio of 2, indicating that the participants in the intervention group RTW twice as quickly compared to the participants in the control group. This Hazard Ratio is based on comparable studies on RTW of workers who are sick-listed and who are receiving sickness benefits [42,43]. Assuming that half of the workers will achieve sustainable RTW during the first 12 months of the follow-up period, and based on a power of (1-β=) 0.80 and a two-sided significance level of 0.05 (α), a sample size of 130 participants (n = 2 × 65) is needed. Based on comparable research, loss to follow-up of 20% is taken into account. This results in 164 participants (n = 2 × 82) to be included in the study. This number of participants seems feasible as samples from the registration database at the SSA indicate that approximately 3000 persons could be invited for participation over a time period of one and a half year.

### Randomisation

Prior to randomisation, we will apply pre-stratification in our inclusion procedure to ensure equal representation of the three subtypes amongst CSs with job loss in our sample; (1) workers whose temporary employment contract ended before or during sick leave; (2) temporary agency workers; and (3) unemployed workers. Randomisation to either the intervention group or control group will be performed on the individual level and will be performed separately for each stratum. Randomisation will be performed by the coordinating researchers (with the exception of the executive researcher), using computerized blocked randomisation by means of the Randomisation Plan Generator [44]. The number of participants in each block will be four, with an allocation ratio of 1:1.

Blinding to the randomisation outcome in this study is not possible due to the nature of the intervention program, in which various stakeholders will need to cooperate to support and guide participants in the intervention group. Furthermore, for practical reasons with regard to usual care, the researchers will have to inform the SSA team and the GP of participants about the inclusion of the participant and the group to which the participant was randomised.

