**Methods/Design:**

This study employs a two-armed randomised controlled trial with a follow-up period of 12 months. The study population (n = 164) will be recruited from a national sample of cancer survivors (18–60 years), who have been sick-listed for 12–36 months. Participants will be randomised by using computerized blocked randomisation (blocks of four). All participants will receive usual care as provided by the Dutch Social Security Agency. Additionally, participants in the intervention group will receive a tailored return to work intervention program, which includes vocational rehabilitation and supportive psychosocial components, as well as (therapeutic) placement at work. The primary outcome measure is duration until sustainable return to work; the secondary outcome measure is rate of return to work. Other parameters include, amongst others, fatigue, coping strategy and quality of life. We will perform Cox regression analyses to estimate hazard ratios for time to sustainable return to work.

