## Methods/Design

### Design/setting

This study employs a two-armed non-blinded randomised controlled trial (RCT) with a follow-up period of 12 months. Data will be gathered using questionnaires at baseline, 3, 6 and 12 months post-study entry. Prior to the start of this study, a focus group study with CSs with job loss and/or unemployment experience was conducted, in order to explore barriers and facilitators they experienced with regard to RTW. We used the results from this focus group study to develop the intervention program that is being evaluated in this study. Design and results of the focus group study will be published separately. The CONSORT statement was used to report the design of this study [18]. The study was approved by the Medical Ethical Committee of the VU University Medical Center (VUmc) and the Scientific Committee of the EMGO+ Institute / VUmc.

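### One published block size of four in each stratum of an open trial could let the central team know up to one third of upcoming allocations

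*Protocol article*

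**What the plan says.** All references are to the protocol article.

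- **Block size.** Under Randomisation: "The number of participants in each block will be four, with an allocation ratio of 1:1". The Methods/Design part of the abstract repeats the block size.
- **Strata.** There are three worker subtypes, and randomisation "will be performed separately for each stratum".
- **Blinding.** Design/setting describes a "two-armed non-blinded randomised controlled trial". Under Randomisation, the researchers must inform the SSA team and the GP "about the inclusion of the participant and the group to which the participant was randomised".
- **Who randomises.** The coordinating researchers do so from a computer-generated plan. The executive researcher is excluded from this step.
- **Order of enrolment.** Under Recruitment of participants, respondents who are not clearly ineligible on the short questionnaire are telephoned and checked against the criteria. Those who qualify are sent the baseline questionnaire and consent form. When both come back, the person is included and allocated. The text then has the GP notified of the inclusion and asked about interfering comorbidities, with a possible joint meeting to agree on participation.
- **Timing.** Study population places candidates still in, or awaiting, intensive treatment on a wait-list until at least six weeks after it ends. The reply postcard lets a candidate ask to be contacted later.

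**The concern.** With a constant, known block size, the arms must balance after every fourth participant in a stratum. Anyone who has followed the earlier allocations can tell when one arm of the current block is full, and then knows the next allocation. Recruitment here is national but run by one research team with only three strata, and that team handles the group assignments. The sequence could therefore be reconstructed centrally. Keeping the executive researcher away from the randomisation protects the list, but it does not prevent deduction from past allocations.

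If the person judging eligibility, or choosing when to call a wait-listed candidate, knew the next assignment, more motivated or healthier candidates could be steered towards one arm. Motivation and health plausibly drive return to work. The confounders that Statistical analysis names as examples are gender, age, stratum and type of cancer. Intention and readiness to return to work are measured, but the article calls them indicators only. Adjustment could not be relied on to undo selective entry. The Discussion covers lack of blinding and self-selection, but not predictability of allocation.

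**Working it through.** **Inputs.** Block size 4, ratio 1:1 and three strata (Randomisation); total 164 and recruitment over one and a half years (Sample size). The article gives no predictability figure. Its total reproduces: 65 per arm / 0.80 = 81.25, rounded up to 82, and 2 × 82 = 164.

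**Certain allocations, fixed blocks of four.** There are six possible blocks. Two (AABB, BBAA) make places 3 and 4 certain. The other four make only place 4 certain.

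- Certain places per block: (2 × 2 + 4 × 1)/6 = 4/3.
- Share: (4/3)/4 = 1/3.
- By place: 0, 0, 1/3, 1.
- Complete blocks: 164/3 = 54.7.
- Assumed strata of 55, 55 and 54, with incomplete last blocks: 55 is 13 blocks plus 3 places, giving 13 × 4/3 + 1/3 = 17.67; 54 is 13 blocks plus 2 places, giving 17.33. Total 17.67 + 17.67 + 17.33 = 52.7.

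**Best guess (name the arm that is behind).** (1/2 + 2/3 + 2/3 + 1)/4 = 17/24 = 70.8%, against 50% with no information.

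**Effect of a gap between decision and allocation.** Take a decision at a random point in the block, with all allocations up to then known.

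- No intervening allocation in the stratum: 1/3.
- One intervening allocation: certainty arises only if two places are already filled (probability 1/4) and both are the same arm (1/3), so that the candidate takes place 4. 1/4 × 1/3 = 1/12 = 8.3%.
- Two or more: 0. Either at least two unknown places of the same block come first, or the candidate falls in a new block.

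**How long is the gap?** The article does not say. Assuming even accrual over 18 months and equal strata, 164/(18 × 3) = 3.0 allocations per stratum per month. With an assumed two to four weeks between telephone call and return of the forms, roughly one to three allocations would intervene. A quick return, or slow accrual in a stratum, brings the exposure back towards one third.

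**Varying block sizes.** Simulation with 55 per stratum, 2,000 runs, and an observer who knows the set of sizes but not their order:

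| Blocks | Certain | Best guess correct |
|---|---|---|
| 4 only | 32.2% | 70.3% |
| 4, 6 | 5.6% | 68.9% |
| 4, 6, 8 | 2.4% | 67.6% |

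The first row sits slightly below the exact 33.3% and 70.8% because the last block is incomplete.

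**The GP step.** Study population makes absence of interfering comorbidities, on the GP's report, a condition of inclusion. Recruitment of participants describes that report after inclusion and allocation, and Randomisation has the GP told the group. As written, part of eligibility can be judged with the group known. Block size plays no part in this.

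**The case against.** A fair defence has several strands.

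- **One third is an ideal observer's figure.** It needs every earlier allocation in the stratum and knowledge of which place the candidate will fill. The candidate largely sets the return date of the forms, so a caller will often not know the place. This stands, and it is why one third is given as a ceiling.
- **Few people could follow the sequence.** A single SSA team or GP sees too few participants. The article does not say who telephones candidates or whether that person follows allocations by stratum, and such detail may be in the full protocol. This stands for SSA teams and GPs. For the central team the possibility remains, because the stated rule is itself the weak element.
- **Much of the timing is not in staff hands.** Asking to be contacted later is the candidate's own choice, and the wait-list follows self-reported treatment. This stands, apart from the latitude left by a six-week minimum with no stated maximum.
- **The remedy barely changes best-guess success.** True: about 71% to about 68%. The gain is in certainty.
- **Baseline measures are collected before randomisation and adjusted analyses are planned.** This mitigates the risk without removing it.

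A reader might infer that about 55 allocations will in fact be known, that concealment is broken, or that the contact-later option and the GP meeting are entry points for steering by block size. The documents do not support this. The postcard choice belongs to the candidate, the GP step follows allocation, and nothing shows that anyone has used or would use the information.

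**Conclusion.** The point holds as an avoidable risk of selection bias; it does not show that bias occurred. In the central research team, up to one third of upcoming allocations (53 to 55 of 164) could be known for certain when a decision on a candidate is taken. This assumes that someone there knows the block size and the ordered earlier allocations in the stratum, and that no other allocation in the stratum intervenes. One intervening allocation reduces the figure to 8.3%, two to zero. The staff decision exposed is the telephone eligibility check, with some room in the timing of wait-listed candidates. No effect on the hazard ratio can be estimated from the documents, and the sample size is unaffected. The change is cheap enough that it should be made. The order of the GP report is a separate weakness that a new block scheme would not cure.

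**What to change.** 1. Under Randomisation and in the abstract, replace the fixed block of four with permuted blocks of randomly varying size (for example 4, 6 and 8) within each of the three strata. Keep the sizes and the sequence from anyone who screens, telephones or schedules candidates, and leave the sizes unpublished until enrolment closes.
2. Separately, under Recruitment of participants, obtain the GP's comorbidity report, hold any consensus meeting, and record eligibility as final before the allocation is released to anyone.

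Make both changes together. Once the GP meeting comes before allocation, it becomes another judgement, shared with the research team, that predictable blocks would expose.

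**Cost.** A newly generated list; a maximum imbalance between arms within a stratum of 4 instead of 2; and, for the second change, a wait for the GP's reply before each allocation. The target of 164 does not change.

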### Statistical analysis

All statistical analyses will be performed according to the intension-to-treat principle. If necessary, the per-protocol principle will also be applied [45]. Descriptive analyses will be performed to check whether there are relevant differences in the baseline characteristics of the intervention and the control group at baseline. Analyses will be performed on an individual level. All analyses will be performed both crude and adjusted for potential confounders, e.g., gender, age, stratum of participants, or type of cancer. Also, these variables will be checked for effect modification. Scores on the included outcomes measures and parameters in the study will be calculated according to published scoring algorithms. The results of the questionnaires will be compared between both groups at baseline and at 3, 6 and 12 months follow-up. Correction for baseline values will be applied.

The primary outcome measure, duration until sustainable RTW in both groups, will be described using the Kaplan-Meier method. We will use the Cox proportional hazard model to estimate hazard ratios and corresponding 95% confidence intervals for sustainable RTW. Finally, we will also perform multiple regression analysis to determine associations between the primary outcome measure and predictor variables, such as fatigue and coping strategy, in order to identify prognostic factors for RTW in this population. A two-tailed significance level of <0.05 is considered statistically significant in all analyses. All analyses will be performed using SPSS 20.0 [46].

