With regard to the sample size, we chose a Hazard Ratio of 2, which is not uncommon for studies in (moderately) comparable populations. Still, this number might be optimistic in terms of the anticipated results. Another limitation is that this study does not use blinding, i.e., we have to disclose to the participant’s RTW team at the SSA whether the participant is in the intervention group or the control group. This could potentially lead to awareness in the SSA teams about their care being evaluated, which could result in a different type of usual care provided to the intervention group compared to the control group. Finally, blinding could prevent contamination of the control group, but as this study recruits 82 participants for the intervention group on a national level, the researchers estimate the risk of contamination of the control group marginal. Potentially, increased awareness of RTW could lead to participants in the control group employing RTW activities on their own, which they might not have done if they were not participating in the study. Enhanced RTW activities in the control group could distort a potential effect of the tailored RTW intervention program and lead to an underestimation of any effect that will be measured between the intervention group and the control group. Finally, it is not unlikely that CSs with job loss feel disappointed in the labour market (due to job loss) or the social security system (due to a lack of appropriate RTW interventions), which may influence their willingness to participate in an experimental study that offers a RTW intervention program. This could potentially lead to selection bias in our sample of participants.

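### The trial is described as non-blinded for reasons that apply only to participants and care providers; deriving the return-to-work event and running the primary analysis could be masked at little cost

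*Protocol article*

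**What the plan says.** Design/setting: "This study employs a two-armed non-blinded randomised controlled trial (RCT) with a follow-up period of 12 months".

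Randomisation: "Blinding to the randomisation outcome in this study is not possible due to the nature of the intervention program". The explanation that follows is that several stakeholders must work together to guide intervention participants, and that "the researchers will have to inform the SSA team and the GP of participants about the inclusion of the participant and the group" to which he or she was allocated.

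Discussion, Methodological considerations: "Another limitation is that this study does not use blinding, i.e., we have to disclose to the participant’s RTW team at the SSA". The section then considers awareness in the SSA teams, contamination of controls, extra activity by controls and selection. It does not consider bias in deriving or analysing the outcome.

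Outcome measures & prognostic factors: the primary outcome is "calculated as the number of days between the day of randomisation and the first day of sustainable RTW", with data collected by questionnaire. "Sustainable RTW is defined as a period of minimum 28 calendar days, during which the CS is working according to schedule". Paid work and work with benefits continuing both count, and sick leave that recurs within four weeks is merged into the initial spell.

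Statistical analysis: all analyses are by intention to treat, each both crude and adjusted. The confounders are given as examples. "If necessary, the per-protocol principle will also be applied".

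**The concern.** Who is masked is a separate question for each role. Participants, coaches, job hunters, SSA teams and GPs cannot be masked here. The person who turns questionnaire answers into an event and a date can be, and so can the analyst. The article makes one general statement about the study and supports it with reasons that fit only the first group.

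This matters because the event is not a plain administrative record. Someone has to read follow-up questionnaires from 3, 6 and 12 months, decide whether a stretch of at least 28 days was worked as scheduled, and fix its first day. If that person knows the arm, borderline cases may be resolved differently in the two arms. Placement at work, including therapeutic placement, is part of the program, so borderline cases may also be more frequent in the intervention arm. With about 65 events planned, there is limited room for error of this kind, and it is a source of bias that the team can control.

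**Working it through.** **1. Reasons against roles.**

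| Role | Reason in the article for knowing the arm |
|---|---|
| Participants, coaches, job hunters | Yes: nature of the program |
| SSA team, GP | Yes: must be told the group for practical reasons of usual care |
| Person deriving the event and its date | None given |
| Analyst of the Cox model | None given |

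The coordinating researchers randomise, with the executive researcher excepted. In Route 1 the researchers assign the job hunting agency. The article does not say who derives events or runs the model.

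**2. The plan's own figure.** Inputs from Sample size: HR 2, power 0.80, two-sided 0.05, half with an event by 12 months, 20% loss.
- Schoenfeld events: 4 × (1.960 + 0.842)² / (ln 2)² = 65.3, rounded up to 66.
- Participants: 66 / 0.50 = 132, against 130 stated. With 65 events the power is 0.798, so the stated figure reproduces within rounding.
- Loss: 65 / 0.80 = 81.25, rounded up to 82 per arm, or 164.

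**3. Sensitivity A: the planned effect is observed and intervention events are moved to non-events.**
- Arm proportions under proportional hazards with HR 2: control survival S satisfies (S + S²)/2 = 0.5, so S = 0.618. Event proportions are 0.382 (control) and 0.618 (intervention).
- Evaluable per arm: 164 × 0.80 / 2 = 65.6. Events: e1 = 40.5 and e0 = 25.1.
- HR = ln(1 − e1/65.6) / ln(1 − e0/65.6); z = ln(HR) / √(1/e1 + 1/e0).

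| Events moved | e1 | HR | z |
|---|---|---|---|
| 0 | 40.5 | 2.00 | 2.73 |
| 3 | 37.5 | 1.76 | 2.20 |
| 4 | 36.5 | 1.69 | 2.03 |
| 5 | 35.5 | 1.62 | 1.85 |

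The 1.96 threshold is crossed at 5, not at 4. Five is 5/40.5 = 12% of intervention events, or 5/65.6 = 8% of all events.

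**4. Sensitivity B: no true effect and intervention non-events are moved to events.** Assumed: 65 analysed per arm, 32.5 events in each, proportional hazards. With k moved, HR = ln(1 − (32.5 + k)/65) / ln(0.5), and the mean of z is √((65 + k)/4) × ln(HR).

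| k | Apparent HR | Two-sided rejection rate |
|---|---|---|
| 0 | 1.00 | 5.0% |
| 2 | 1.09 | 6.5% |
| 4 | 1.19 | 11% |
| 6 | 1.29 | 19% |
| 8 | 1.41 | 31% |

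The document gives no misclassification rate. Both tables show a range of what-if values and do not estimate bias.

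**The case against.** The strongest reply is that this is mostly silence. Who codes events and whether the analyst sees coded arms often belong in a full protocol or analysis plan. The blinding sentences are also explained by care delivery, where they are correct. Part of this stands: nothing in the article declares masked analysis impossible, and a plan not shown could provide for it. What remains is that the trial is called non-blinded without qualification in Design/setting, and the reasons given do not reach the two steps that could be masked.

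A reader might infer more than the text supports:

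- *That researchers who know the arm decide the events.* No passage says who does this.
- *That the endpoint is wide open.* The outcome section already settles the four-week recurrence rule and that work with therapeutic conditions counts. What is left is mainly working to schedule and the first day, and much of that is the participant's own report.
- *That analysis choices could replace the primary result.* Intention to treat is fixed, crude results accompany adjusted ones, and per-protocol is only additional. Open covariates are a pre-specification matter more than a blinding one.
- *That three or four reclassifications overturn the test.* At four, z is still 2.03. It takes five, all in one direction.

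It also stands that masked coding cannot remove reporting bias from participants who know their arm.

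**Conclusion.** The point holds as an inexpensive improvement to the stated design; it is not a demonstrated bias or a fatal flaw. The article's reasons justify leaving participants, SSA teams, GPs and program providers unmasked, and no one else. Since the primary event is built mainly from questionnaires and keeps some judgement, arm-aware derivation would be an avoidable risk.

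The size of that risk cannot be derived from the document. The sensitivities rest on HR 2, 50% events overall, 20% loss, proportional hazards and reclassification in one direction within one arm. On those terms, five moved intervention events take z from 2.73 to 1.85. The margin would be thinner if the observed effect were smaller, and the Discussion itself calls HR 2 possibly optimistic. The sample size is unaffected.

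**What to change.** 1. In Randomisation, limit the statement that blinding is not possible to participants, SSA teams, GPs and program providers. Align Design/setting and the Discussion with it.
2. Have an existing team member who takes no part in allocation or in assigning job hunting agencies derive sustainable return to work and its first day. The source would be the work section of the questionnaires and, where available, SSA extracts, with arm and program fields removed.
3. Lock the event list and the adjustment covariates before the allocation code is linked, and run the primary Cox analysis on coded arms.
4. Write the per-protocol criteria before linkage. The per-protocol set itself need not be built masked, because program adherence exists only in the intervention arm.
5. State as a limitation that outcomes are self-reported by unmasked participants.

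Cost: a little extra data handling, with no additional participants or data collection. The gain is partial: some work answers may still reveal the arm, and self-report bias remains.
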